
### Study endpoints

Here we provide a summary of the endpoints assessed in this study. A detailed list with characterization of the variables can be found online (10.5281/zenodo.5556317).

#### CSF-Hb (biomarker)

CSF-Hb constitutes the biomarker assessed in this study. CSF-Hb levels (oxyhemoglobin) will be quantified in the CSF samples obtained from patients after aSAH using spectral deconvolution, as described previously [12, 13].

#### Primary endpoint

The primary endpoint of this study is the occurrence of SAH-SBI during the monitoring period. SAH-SBI is a categorical variable that will be derived as a composite from the categorical secondary endpoints aVSP, DCI, and DIND: If any one or more of the three secondary endpoints (aVSP, DCI, or DIND) is present on the corresponding day, SAH-SBI is considered to be present. If neither information on aVSP (no imaging performed), nor DCI (no imaging performed) or DIND (patient not clinically assessable) could be obtained, SAH-SBI is considered to be non-assessable. In any other instance, SAH-SBI is considered not to be present.

#### Secondary endpoints

Secondary endpoints, which will be assessed during the first 14 days post-SAH on a daily basis, are: angiographic vasospasms (aVSP), delayed cerebral ischemia (DCI), delayed ischemic neurologic deficits (DIND), elements of triple H therapy, spasmolysis, surgical decompression.

The definition of aVSP comprises a narrowing of cerebral arteries based on a DSA, CTA or MRA. In the absence of an appropriate imaging procedure on the respective day, this will be noted as *no imaging performed*. Categorical variable [present, absent or no imaging performed].

DCI is defined as new perfusion deficit or new infarction in native and/or contrast-enhanced CT/MRI. In the absence of an appropriate imaging procedure on the respective day, this will be noted as *no imaging performed*. Categorical variable [present, absent or no imaging performed].

DIND is defined as a new focal neurological deficit or a decrease in GCS of at least 2 points for at least 2 hours. In case the patient cannot be clinically assessed (e.g., sedation), this will be noted as *non-assessable*). Categorical variable [present, absent or non-assessable].

Secondary endpoints, which will be assessed at the 12 weeks (+/− 2 weeks) follow-up: Chronic hydrocephalus, Glasgow Outcome Scale Extended (GOSE), modified Rankin Scale (mRS).

#### Safety endpoints

Safety endpoints, which will be assessed during the first 14 days post-SAH on a daily basis in the afternoon, always at approximately the same time: CSF infection, revision due to surgical site infection at the EVD skin entrance.

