#### Post-SAH monitoring

CSF sampling and clinical assessments will be performed on a daily basis between day 1 and day 14 post-SAH, always at approximately the same time of the day (CSF sampling in the morning, clinical assessment in the afternoon) by a trained member of the clinical study team.

CSF sampling will be performed via EVD or LD if present. The decision regarding the insertion of an EVD or LD is made on a clinical basis by the treating physician independently of this study. If an EVD or LD is present, 2 ml of CSF will be sampled daily, centrifuged at 1500 G for 15 minutes, and subsequently stored at − 80 °C.

The clinical assessment of patients for the primary and secondary endpoints will be blinded to CSF sampling, since the macroscopic aspect of CSF after centrifugation may provide an indication of the CSF-Hb level. The definition of aVSP comprises a narrowing of cerebral arteries based on a DSA, CTA or MRA. In the absence of an appropriate imaging procedure on the respective day, this will be noted as *no imaging performed*. DCI is defined as a new perfusion deficit or a new infarction in native and/or contrast-enhanced CT/MRI. In the absence of an appropriate imaging procedure on the respective day, this will be noted as *no imaging performed*. DIND is defined as a new focal neurological deficit or a decrease in GCS of at least 2 points for at least 2 hours. In case the patient cannot be clinically assessed (e.g., under sedation), this will be noted as *non-assessable*). Other secondary endpoints assessed include elements of triple H therapy, spasmolysis, and surgical decompression. CSF infection and revision due to surgical site infection at the EVD skin entrance comprise safety endpoints.

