The collection of CSF samples for the HeMoVal study is a manipulation at the closed EVD/LD drainage system, which may raise concerns about an increased risk for CSF infections. Reported infection rates of EVD/LD systems in clinical routine range from 0 to 32%. However, rates around 10% are usually described [21–23]. Since the introduction of antimicrobial-coated catheters, infection rates of less than 2% have been reported at many centers [24–29]. The single most important risk factor for CSF infection in patients with EVD/LD is the duration of external CSF diversion [21, 23, 30–32]. This factor is not influenced by the HeMoVal study, since the indications for insertion and removal of CSF diversion devices are made independent of the study exclusively based on clinical criteria assessed by the independent treating physician (e.g., increased intracranial pressure, need for pressure monitoring). The HeMoVal study increases the number of manipulations of the EVD/LD system compared to clinical routine due to the daily sampling regimen. Evidence regarding the existence, strength, and causality of an association between such manipulations and the incidence of CSF infections is sparse and inconclusive [21, 23, 30–39], but theoretically an increased risk of infection with each manipulation must be assumed. However, strict adherence to aseptic techniques limits this risk to an absolute minimum [40–42]. In a prospective single center observational study involving 47 patients, adhering to the same protocol as the HeMoVal study, only one patient (2.1%) developed CSF infection [12]. This lies in the lower range of recent reports on the incidence of CSF infections in patients with EVD/LD [24–29]. We therefore consider the additional risk of CSF infection due to repetitive sampling under aseptic measures in this study to be minimal. However, CSF infection is included as a safety endpoint in the assessment during the monitoring period*.* Further, we don’t expect an increased risk of symptomatic CSF overdrainage due to the sampling regimen in the HeMoVal study, since the collected 2 ml of CSF per day represent only a fraction of the regular hourly drainage volume needed for the treatment of posthemorrhagic hydrocephalus [22] and because the total daily drainage volume remains unchanged. Overall, we consider that the potential scientific insights and clinical implications of the HeMoVal study clearly outweigh its risk.

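### Scheduled infection capture ends on the last possible sampling day, and the site-infection endpoint names only the EVD entrance although lumbar drains are sampled too

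*Protocol article*

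**What the plan says.** **Window.** The protocol article, Safety endpoints, states: "Safety endpoints, which will be assessed during the first 14 days post-SAH on a daily basis in the afternoon". The two endpoints are "CSF infection, revision due to surgical site infection at the EVD skin entrance". Table 1 places both under the monitoring period, which ends at day 14 at the latest. Post-SAH monitoring sets the same window for sampling: "CSF sampling and clinical assessments will be performed on a daily basis between day 1 and day 14 post-SAH".

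**Later contact.** The visit at 12 weeks (plus or minus 2 weeks) records chronic hydrocephalus, GOSE and mRS (Secondary endpoints; Follow-up; Table 1). Infection is not among the items. The visit may be done by telephone.

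**Devices.** Post-SAH monitoring says "CSF sampling will be performed via EVD or LD if present", and then "CSF infection and revision due to surgical site infection at the EVD skin entrance comprise safety endpoints". The Table 1 row reads only surgical site infection, with no device named. CSF infection carries no device limit anywhere.

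**Serious events.** This section covers adverse events that may be attributable to sampling and that meet a seriousness criterion. It states no day limit and no device limit.

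**Discussion of risk.** The Discussion accepts that, in theory, each manipulation adds infection risk. It also says "The single most important risk factor for CSF infection in patients with EVD/LD is the duration of external CSF diversion" and that the study does not alter this duration. It cites rates of 0 to 32%, usually around 10%, and for references 24–29 says that "infection rates of less than 2% have been reported at many centers". Of the 47-patient pilot it says "only one patient (2.1%) developed CSF infection". It places that figure towards the bottom of the reports in references 24–29 and concludes that the added risk is minimal.

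**The concern.** Infection from repeated handling of the drain is the main study-related harm that the Discussion weighs. If each manipulation is assumed to add risk, patients still being sampled on day 14 have had the most added risk, and scheduled observation of them ends on that day. Sampling is in the morning and assessment in the afternoon, so the last possible sample has only hours of scheduled follow-up.

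LDs are sampled under the same daily regimen, and the LD cohort is an analysis population of its own. A site endpoint worded for the EVD entrance gives that cohort no site-infection count, unless sites follow Table 1 instead.

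At stake is the completeness of the study's safety count. With up to 250 EVD patients, the study can estimate the infection rate far more precisely than the pilot did, but only if late events are captured.

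**Working it through.** **1. Capture window against sampling window**

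| Item | Day 1 to 14 | After day 14 |
|---|---|---|
| Study CSF samples, EVD or LD | daily while a drain is present | none |
| CSF infection, either drain | daily | no scheduled item |
| Site infection, EVD entrance | daily | no scheduled item |
| Site infection, LD entrance | not in the two text definitions; Table 1 row names no device | no scheduled item |
| Serious event possibly due to sampling | yes | yes, if a seriousness criterion is met |

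The scheduled windows for sampling and for infection coincide, so the follow-up after a sample shrinks to zero full days by day 14.

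**2. How large the gap could be**

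The documents give no lag between a contaminating sample and a detected infection, and no distribution of drain duration. For illustration only, assume a lag of L days. An infection from a sample on day d is detected on day d + L and is missed if d + L > 14. In a patient sampled on all 14 days this applies to the last L sampling days, a share of L/14:

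- L = 3: 3/14 = 21%
- L = 7: 7/14 = 50%

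This is a share of sampling days, not of infections. It falls to zero for a patient whose last sample is on or before day 14 − L. With L = 7, a patient last sampled by day 7 loses nothing.

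**3. The pilot figure**

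- Stated rate: 1/47 = 0.0213, so the 2.1% reproduces.
- Exact (Clopper-Pearson) 95% interval: the lower limit is the 0.025 quantile of Beta(1, 47) = 0.0005; the upper limit is the 0.975 quantile of Beta(2, 46) = 0.113. The interval is 0.05% to 11.3% (Wilson: 0.4% to 11.1%).
- The interval includes the rate of around 10% that the Discussion calls usual, but only near its edge. If the true rate were 10%, P(X ≤ 1) = 0.9^47 + 47 × 0.1 × 0.9^46 = 0.044. At a true rate of 5% it is 0.312, and at 2% it is 0.758.
- 2.1% lies near the bottom of 0 to 32%. It is not below 2%, so it does not fit as a low value among reports summarised as less than 2%. The difference is 0.1 percentage point on a single event.
- The pilot rate is a total rate with no comparison group. It cannot by itself estimate the additional risk from sampling.

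**4. What this study could deliver**

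For illustration, 5 infections in 250 EVD patients (2%) would give an exact 95% interval of 0.7% to 4.6%, against 0.05% to 11.3% from the pilot.

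**The case against.** Much can be said for the plan, and several stronger readings fail.

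- **Safety reporting does not stop altogether at day 14.** The serious-event definition has no day or device limit, so a late CSF infection that prolongs the stay could fall under it. That stands. But it depends on seriousness and on a judgement about attribution, and it is not a question put to every patient, so it cannot give a complete count.
- **Safety capture is not confined to the EVD.** CSF infection, the main risk discussed, is counted for both drains. Nor is it shown that LD site infections will be lost: the Table 1 row is open as to device, and detailed variable definitions are in an online document not shown here. What stands is narrower: the text states a restricted definition twice and the table an unrestricted one once.
- **The pilot's 2.1% does not contradict the cited literature range.** It lies within 0 to 32%. The tension is only with the figure below 2%, and a statement about many centers leaves room for higher rates in some of references 24–29, which cannot be checked here.
- **The minimal-risk conclusion does not rest on one event in 47 alone.** The Discussion also relies on aseptic technique and on unchanged drain duration, and concedes a theoretical risk. A missing interval in a discussion paragraph is a reporting matter.
- **How infection rates are analysed** is left to the statistical analysis plan, which is not shown, so nothing is raised on that.

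**Conclusion.** The point holds in a limited form, as an inexpensive improvement. Scheduled capture of CSF and site infection closes on the last possible sampling day, with no infection item afterwards, so non-serious infections after late samples are not systematically counted. The site endpoint is worded for the EVD entrance although LDs are sampled, and this does not match Table 1.

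The size of the under-count cannot be derived from the documents. The ceiling of 21% to 50% of sampling days rests on an assumed lag of 3 to 7 days and on sampling every day to day 14. It should not be read as a proportion of infections missed.

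The Discussion sentence on the pilot is a wording issue. One event in 47 is imprecise, but it is not evidence of a higher risk. The primary association analysis is unaffected.

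**What to change.** 1. **Late infections.** Add one item at the existing 12-week contact: any CSF infection or drain-site infection after day 14, with date and device. Where the contact is by telephone, check the answer against hospital records.
2. **Site endpoint.** Reconcile Safety endpoints and Post-SAH monitoring with Table 1, so that the endpoint covers the skin entrance of an EVD or an LD. Check the online variable list for the same wording.
3. **Discussion wording (minor).** Report the pilot as 1/47 = 2.1% (exact 95% interval 0.05% to 11.3%), and reconcile its placement among references 24–29 with the rate below 2% given for the same references.

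The cost is one or two eCRF fields, some record checking, and possibly a higher reported infection rate. No visit, sample or procedure is added. Patients already past their 12-week contact when the item is introduced would need a check of their records.

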#### Demographic/baseline measures

Measures assessed at the time of study inclusion (usually within 24 hours of hospital admission): Patient demographics (age, sex), medical history (antithrombotics, diabetes, hypertension, coronary artery disease, smoking), clinical assessment (Glasgow Coma Scale (GCS), pupil status, cranial nerve deficit, focal neurological deficit, headache, neck stiffness), clinical SAH scores at admission (World Federation of Neurological Surgeons (WFNS), Hunt & Hess grade), Radiological features (aneurysm location, aneurysm size, intracerebral hemorrhage, intraventricular hemorrhage, hematoma volume), radiological SAH scores at admission (modified Fisher grade, Barrow Neurological Institute (BNI) grade), aneurysm therapy.

### Study assessments

A detailed definition and description of each variable, including levels (for factors) and range (for continuous variables), and assessment procedure, can be found online (10.5281/zenodo.5556317). It is ensured that all members of the clinical study team will be specifically trained in the study-specific assessments. The assessments in this study are divided into *baseline assessment*, *post-SAH monitoring*, *3-months follow-up*, and *measurements*. Table 1 shows the assessment schedule, the study flowchart is given in Fig. 2.

**Table 1 Tab1:** HeMoVal study assessment table. Overview of the different study periods (enrollment, baseline assessment, monitoring, 3-months follow-up, measurements) with the corresponding time schedule and assessments

Study periods	Enrollment	Baseline assessment	Monitoring	3-months follow-up	Measurements
**Time**	Hospital admission	Study inclusion	Daily after inclusion for max. 14 days postSAH	+ 12 weeks after event (+/− 2 weeks)	N/A
**Eligibility Criteria**	x				
**Patient information & consenting**	x				
**Demographic/baseline measures**		x			
**CSF-sampling**			x (daily, if EVD/LD)		
**aVSP**			x (daily, if imaging)		
**DCI**			x (daily, if imaging)		
**DIND**			x (daily, if assessable)		
**Spasmolysis**			x (daily)		
**Intracerebroventricular rtPA**			x (daily)		
**Triple H therapy**			x (daily)		
**Surgical decompression**			x (daily)		
**Nimodipine therapy**			x (daily)		
**CSF infection**			x (daily)		
**Surgical site infection**			x (daily)		
**Chronic hydrocephalus**				x	
**GOSE**				x	
**mRS**				x	
**Hematoma volume**					x
**CSF-Hb**					x

**Fig. 2 Fig2:**
[figure not shown]
HeMoVal study assessment flowchart: Graphical representation of the different phases of assessment (enrollment, baseline assessment, monitoring, 3-months follow-up), measurements and analysis in the HeMoVal study

#### Baseline assessment

Gathering of demographic (age, sex) and baseline (medical history, clinical assessment, clinical SAH scores at admission, radiological features, aneurysm therapy) patient data. Performed directly after study inclusion by a trained member of the clinical study team.

#### Post-SAH monitoring

CSF sampling and clinical assessments will be performed on a daily basis between day 1 and day 14 post-SAH, always at approximately the same time of the day (CSF sampling in the morning, clinical assessment in the afternoon) by a trained member of the clinical study team.

CSF sampling will be performed via EVD or LD if present. The decision regarding the insertion of an EVD or LD is made on a clinical basis by the treating physician independently of this study. If an EVD or LD is present, 2 ml of CSF will be sampled daily, centrifuged at 1500 G for 15 minutes, and subsequently stored at − 80 °C.

The clinical assessment of patients for the primary and secondary endpoints will be blinded to CSF sampling, since the macroscopic aspect of CSF after centrifugation may provide an indication of the CSF-Hb level. The definition of aVSP comprises a narrowing of cerebral arteries based on a DSA, CTA or MRA. In the absence of an appropriate imaging procedure on the respective day, this will be noted as *no imaging performed*. DCI is defined as a new perfusion deficit or a new infarction in native and/or contrast-enhanced CT/MRI. In the absence of an appropriate imaging procedure on the respective day, this will be noted as *no imaging performed*. DIND is defined as a new focal neurological deficit or a decrease in GCS of at least 2 points for at least 2 hours. In case the patient cannot be clinically assessed (e.g., under sedation), this will be noted as *non-assessable*). Other secondary endpoints assessed include elements of triple H therapy, spasmolysis, and surgical decompression. CSF infection and revision due to surgical site infection at the EVD skin entrance comprise safety endpoints.

#### Follow-up

The assessment will be performed at the 12 weeks (+/− 2 weeks) follow-up visit. This will be done on site if possible. If this is not possible, a consultation by telephone will be conducted. The presence of chronic hydrocephalus is defined as the dependence on permanent CSF diversion which was not present before aneurysm rupture. The functional status scores will be assessed with the Glasgow Outcome Scale Extended (GOSE) and the modified Rankin Scale (mRS).

#### Measurements

CSF-Hb measurements and hematoma volumetry will be performed after completion of the monitoring period of the last included patient in this study.

CSF-Hb measurements: CSF-Hb measurements will be performed centralized in the Preclinical Research in Internal Medicine (PRIME) Laboratory, Schlieren, Switzerland. Absorption spectra in the visual range between 350 and 650 nm will be measured and quantification of the oxyhemoglobin in CSF will be performed using spectral deconvolution, as described previously [12, 13]. CSF-Hb measurements are performed by a person blinded to the patients demographic/baseline measures and their clinical assessment/endpoints.

Hematoma volume: Assessed on the initial CT scan of each patient. The CT scan will be uploaded by the local investigators in coded form (identifying information replaced by patient ID) to a HIPAA compliant platform (Lumi, Augmedit bv, Naarden, the Netherlands), from where automated centralized quantification of hematoma volume is performed. The quantification of the hematoma volume is performed by a person blinded to the patient’s CSF sampling/CSF-Hb values and their clinical assessment/endpoints.

#### Serious events

A serious event is defined as any adverse event where it cannot be excluded, that the event is attributable to the sampling of biological material or the collection of health-related personal data, and which:requires inpatient treatment not envisaged in the protocol or extends a current hospital stay,results in permanent or significant incapacity or disability, oris life-threatening or results in death.

If a serious event occurs, the research project will be interrupted. The responsible Ethics Committee(s) and Competent Authority will be notified according to the locally relevant regulations, if required.

### Data management and quality assurance

#### Quality measures

For quality assurance representatives of the responsible Ethics Committee may visit the research sites. Direct access to the source data and all project related files and documents will be granted on such occasions. Central and on-site monitoring (CTU Berne, Switzerland) will be part of the quality control activities implemented for this study. During the study, the central data monitor will check the eCRFs on a weekly basis and lock complete visits. All involved parties will keep participant data strictly confidential.

#### Data recording and source data

The CRFs in this trial are implemented electronically using a dedicated electronic data capturing (EDC) system (REDCap, https://www.project-redcap.org/). The EDC system was activated for the study after successfully passing a formal test procedure. All data entered in the CRFs are stored on a Linux server in a dedicated mySQL database. Responsibility for hosting the EDC system and the database lies with CTU Berne. The initial CT scan of each patient will be uploaded and stored for the duration of the study in coded form (identifying information replaced by patient ID) on the HIPAA compliant platform *Augsafe*. The data from the CSF-Hb analysis are recorded in the EDC system of the Preclinical Research in Internal Medicine (PRIME) Laboratory, Schlieren, Switzerland. For the statistical analysis, the data will be merged to an export of the eCRF, based on the patient ID. Source data will be available at each study site in the respective patient files, either electronically or on paper. The source data will include the original documents relating to the study, as well as the medical treatment and medical history of the patients. In the Investigator Site File and Trial Master File the informed consent forms and other relevant study-specific documents will be recorded. Any patient files and source data will be archived for the longest possible period of time according to the feasibility of the investigational site.

